#### Exclusion criteria

Cases with insufficient material to perform HPA-1a typing by ELISA.Cases with known HPA-1a alloimmunisation.

### Participating centres

All obstetric care centres, hospitals, midwifery practices as well as general practices that provide obstetric care, in the Netherlands, are able to enrol pregnant women to participate in the HIP study. In order to ensure that obstetric caregivers were equipped to inform and counsel pregnant women, communicatory symposia were organised at six locations all over the Netherlands. Additionally, an informational leaflet was produced in different languages (Dutch and English on paper; Spanish, Arabic, Turkish and Polish digitally available; online supplementary material 1). Two informational videos were made informing on FNAIT as well as the HIP study. Finally, a website was created containing news and information about the HIP study (www.HIPstudie.nl).

10.1136/bmjopen-2019-034071.supp1Supplementary data

### Study outcomes

The main study parameters/primary endpoints are

Incidence of HPA-1a negativity in the RhD-negative or Rhc-negative pregnant population in the Netherlands at 27 weeks of pregnancy.Incidence of HPA-1a alloantibodies in the tested population at 27 weeks of pregnancy.Incidence of clinically relevant HPA-1a-mediated FNAIT; classified as mild or severe FNAITSevere FNAITICH.Internal organ haemorrhage.Mild FNAITNeonatal bleeding signs other than ICH or internal organ haemorrhage: haematoma, bruising, petechiae, purpura, mucosal or visceral bleeding.Thrombocytopenia for which treatment was administered (platelet transfusion or IVIg) or for which clinical observation was performed.

Our secondary study parameters/endpoints are:

Neonatal treatment for thrombocytopenia: platelet transfusion (with random-donor platelets vs compatible platelets), IVIg, RBC transfusion.Neonatal morbidity: small for gestational age, infection, hours/days in hospital (neonatal intensive care unit vs medium care), need for additional treatment, congenital abnormalities, other causes causing increased bleeding tendency.Neonatal laboratory findings: platelet count, haemoglobin, C-reactive protein.

### HIP study procedure

As part of the prenatal screening programme for erythrocyte immunisation, an EDTA tube of blood of RhD-negative and Rhc-negative pregnant women will be sent to Sanquin at 27 weeks gestation. These women are eligible for enrolment in the HIP study and will be informed about the study and asked for consent by their obstetric caregivers. This consent or decline of participation is added to the regular laboratory request form for the 27th week assessment, that is, already sent to Sanquin with each tube of blood. No additional blood will be drawn for the HIP study. Once the tubes of blood are sent to Sanquin, the consent is either received digital or on paper, depending on the route and location (various hospitals, midwifery practices and local laboratories).

The procedures that are performed after consent and enrolment in the HIP study can be divided into four separate phases, depending on the time in and after pregnancy (figure 1).

**Figure 1 F1:**
[figure not shown]
Schedule of selection, enrolment and tests in the HIP study. HIP, HPA-screening in pregnancy; HPA, human platelet antigen; PSIE, prenatal screening of infectious diseases and erythrocyte immunisation; RhD, rhesus D; Rhc, rhesus c.

#### Phase I

After regular screening, authorisation and correspondence of the results for the prenatal screening programme for erythrocyte immunisation, the tubes are made available for the HIP study. For the HIP study, the platelet-containing plasma of the stored blood tubes is serologically typed for HPA-1a, using a sandwich ELISA. In short, 20 µL of plasma containing platelets will automatically be pipetted into microtiter plates that have been coated with a monoclonal antibody CLBthromb/1 (C17) directed against glycoprotein IIIa, at a concentration of 3 µg/mL to capture all platelets from the plasma. Then horseradish peroxidase-conjugated (HRP-conjugated) B2G1, an antibody targeting HPA-1a, will be added and plates will be centrifuged and incubated for 45 min. Finally, after washing of the plates, HRP-substrate solution will be added for 15 min, and after stopping of this reaction, the reactions will be quantified using an ELISA reader (Biochrom Anthos, Cambridge, UK). This HPA-1a ELISA was specifically designed for the HIP study, thus for quick and high-throughput screening. All samples with an ELISA value below a defined optic density are called HPA-1a negative. The HPA-1a typing result is supported with an allelic discrimination PCR assay. Plasma and buffy coat of samples that are typed HPA-1a negative will be stored at −20°C, using only a study number. Additionally, for each HPA-1a negative case, material of one HPA-1a positive control will be stored simultaneously.

Because this first phase comprises serological HPA-1a typing, which is performed with fresh material, and a delay in the arrival of consent forms might exist, this phase is performed with all samples from pregnant women who did not decline participation for the HIP study. All consecutive phases, such as antibody screening, risk-assessment development and clinical data retrieval, are solely performed in case of informed consent for the HIP study.

#### Phase II

Of all samples stored with consent, obstetric caregivers will be contacted to obtain clinical information. An overview of these clinical parameters is provided in figure 2. The clinical data will be stored in a secured digital database, designed by the Leiden University Medical Centre (LUMC), called ProMISe. First, study numbers of HPA-1a negative cases and HPA-1a positive controls with corresponding obstetric caregivers are entered into the database. Then, for each case, ProMISe randomly generates a code. Thereafter, obstetric caregivers will receive a secured digital invitation to add clinical data to a digital case report form (CRF) for the cases from their practice. This secured invitation contains the initial personal data for the sample sent for the erythrocyte immunisation screening programme together with the code generated by ProMISe (Project Manager Internet Server). This unique code can be entered online by the caregiver to open the digital CRF and fill in the clinical data. Clinical data are stored in ProMISe, only by anonymous study codes. This way, no personal information is being transferred or entered in our database, nor is the obstetric caregiver in possession of a key that links the anonymous study number to personal information, nor does the caregiver know whether their patients or clients are HPA-1a negative or positive.

**Figure 2 F2:**
[figure not shown]
Clinical parameters. These clinical parameters will be collected in the human platelet antigen-screening in pregnancy study. CRP, C-reactive protein.

#### Phase III

The next step is to evaluate the incidence of alloimmunisation. Of all HPA-1a negative women who gave consent for the HIP study, we will use the stored left-over plasma to screen for HPA-1a alloantibodies. For antibody screening, the Pak Lx assay, a qualitative immunoassay, will be used, according to the manufacturers’ recommendations (LIFECODES Pak Lx Assay, Immucor GTI Diagnostics, Norcross, USA). In short, plasma samples are incubated with reconstituted beads and for the removal of unbound antibodies, the beads are washed. Next a conjugate (antihuman IgG antibody conjugated to phycoerythrin) is added and incubated with the sample for 30 min at room temperature. Finally, the Luminex 200 instrument is used to analyse the data. The advantage of this assay is that it is quick and uses only a small amount of plasma, so there will be enough left-over for further testing in phase IV.

#### Phase IV

Combining the results from phase II to phase III will enable us to select cases of alloimmunisation with and without clinical manifestations of FNAIT to identify possible parameters to predict the development of (severe) bleeding complications. For this, we will be testing different laboratory parameters as well as clinical parameters (figure 2). Laboratory parameters that will be tested to assess risk at bleeding complications are HLA-DRB3*0101 status, antibody level, Fc-core glycosylation and FcγRIII-binding index, endothelial cell binding, endothelial cell function.^24–28^

### Sample size calculation

The HIP study was designed to assess the incidence of clinical relevant FNAIT in pregnant women in the Netherlands. Therefore, the incidence of ICH in HPA-1a immunised cases was compared with HPA-1a positive women. The estimated risk of ICH in immunised cases was 3%. For our power calculation, we took a marge of 1% on the estimated incidence of ICH in FNAIT.^19^
^29^ In our control group, we assumed a risk on symptomatic ICH of 4.9 in 10.000 (0.05%).^30^ To achieve a power of 80% at an alpha level of 5%, we calculated that a total study population of 2400 pregnant women is needed. Within this calculation, we took into account the unequal distribution between HPA-1a positive controls and immunised cases. We considered 5% of our total study population consists of immunised cases, which means that we needed to include 120 immunised cases. Calculations were performed using logistic regression model making use of PASS sample size software 11.

Each year, approximately 60 000 RhD-negative or Rhc-negative pregnant women participate in the prenatal screening programme for erythrocyte immunisation and are therefore eligible for enrolment in the HIP study. To include 120 immunised cases, we need to include 1200 HPA-1a negative women (immunisation rate of approximately 10%).^29^ Because 2.1% of the Caucasian population is HPA-1a negative, the total study population should exist of 60 000 pregnant women (table 1). Based on the previous experience with earlier nationwide research on the detection and prevention of pregnancy immunisation (Opsporing en Preventie Zwangerschaps Immunisatie, OPZI studie in Dutch) and the highly positive attitude towards potential HIP women expressed in our previous study, the expected enrolment was 50%.^31 32^ This would correspond with a study period of 2 years.

**Table 1 T1:** Estimated cases in HIP study

	%	Incidence	Cases in the Netherlands Total pregnancies n=1 70 000	Cases during study period Total included n=60 000*
HPA-1a negative	2.1	1:50	3570	1260
HPA-1a antibodies	10	1:400	428	126
Severe FNAIT	30	1:1300	129	36
ICH	10–30	1:12 500	13	3–4

*Assuming 50% enrolment of the 60 000 RhD/Rhc negative women each year, for 2 years.

FNAIT, fetal and neonatal alloimmune thrombocytopenia; HIP, HPA-screening in pregnancy; HPA, human platelet antigen; ICH, intracranial haemorrhage.

### Statistical analysis

Clinical data will be entered into a validated data capture system, provided and designed by the LUMC. The system is protected by password and contains internal quality checks to identify inaccurate or incomplete data. Laboratory data will be entered in a separate password-protected database by independent technicians, inaccessible to the researchers. Both clinical and laboratory data will be combined and further data management and analysis will be performed using SPSS V.23.0 and Graphpad V.8.0. An interim analysis after 1 year will be performed.

### Ethics and dissemination

The introduction of an antenatal screening programme requires a careful balance between benefit and potential harm. To investigate the true natural history of FNAIT, we aimed to collect data from pregnancies without additional interventions based on screening test results. This observational non-intervention design is ethically challenging. It would be unethical to share the antibody screening results with pregnant women but withhold them from therapy, therefore antibody screening will be performed far after due date. There will be no direct beneficial effect for pregnant women participating in the HIP study, pregnant women will be informed by their caregivers about this before they give consent to our study. Ethical approval for this study has been obtained from the Medical Ethical Committee Leiden-The Hague-Delft (P16.002).

Patient recruitment started in March 2017 and the study is planned to close to recruitment on the spring/summer of 2019. However, to ensure the inclusion of 1000–1500 HPA-1a negative women, the inclusion period might take longer. Accurate predictions on the duration of the study will be made after interim analysis at 1 year. Results will be published in relevant scientific journals and be disseminated in international conferences when inclusion and clinical data collection is finished.

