### Study design

The HIP study is a nationwide prospective and observational cohort study, conducted in all settings of obstetric care in the Netherlands, for a period of 2.5 years.

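### The inclusion goal of 1000–1500 HPA-1a negative women lets recruitment close below the 1200 that the sample size calculation requires

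*Protocol article*

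**What the plan says.** The Sample size calculation section of the protocol article sets the target in three steps. First: "To achieve a power of 80% at an alpha level of 5%, we calculated that a total study population of 2400 pregnant women is needed". Then: "We considered 5% of our total study population consists of immunised cases, which means that we needed to include 120 immunised cases". Then: "To include 120 immunised cases, we need to include 1200 HPA-1a negative women (immunisation rate of approximately 10"%). It divides by an HPA-1a negative prevalence of 2.1% and arrives at 60 000 women to be included. Table 1 shows 1260 HPA-1a negative women and 126 with antibodies from those 60 000.

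The Ethics and dissemination section gives the start of recruitment (March 2017) and the planned close (spring/summer 2019), and adds a second target: "to ensure the inclusion of 1000–1500 HPA-1a negative women, the inclusion period might take longer". It says that the duration will be predicted more accurately after an interim analysis at 1 year. It does not mention the 1200 or say why a range is used.

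**The concern.** A sample size requirement and a recruitment goal for the same group of women should agree, or the text should say why they differ. Here the goal starts at 1000, below the 1200 presented as needed. A team working from the Ethics and dissemination section could close at 1000 and consider the goal met, while the Sample size calculation section would count the study as short.

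At stake is the number of immunised pregnancies. They carry the ICH comparison on which the study was sized, and they are the source of samples for the later risk model. Table 1 expects only 3–4 ICH cases, so there is little room to lose any.

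**Working it through.** **Inputs, all from the Sample size calculation section unless noted.** Total 2400; immunised share 5%; immunisation rate about 10%; HPA-1a negative prevalence 2.1%; 60 000 included; ICH risk 3% in immunised cases; ICH risk 4.9 in 10 000 (0.049%) in controls; alpha 5%. The inclusion goal of 1000–1500 comes from Ethics and dissemination. The storage of one HPA-1a positive control per HPA-1a negative woman comes from Phase I of the study procedure.

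**Step 1: the plan's own chain.**
- Immunised cases needed: 2400 × 0.05 = 120.
- HPA-1a negative women needed: 120 / 0.10 = 1200.
- Yield of 60 000 included: 60 000 × 0.021 = 1260 negative; 1260 × 0.10 = 126 immunised.

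The 1200 and the Table 1 counts reproduce exactly.

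**Step 2: the ends of the inclusion goal.**
- 1000 × 0.10 = 100 immunised; shortfall 120 − 100 = 20; 20 / 120 = 17%.
- 1500 × 0.10 = 150 immunised.
- Expected ICH at 3%: 100 × 0.03 = 3.0, against 120 × 0.03 = 3.6.
- Binomial chance of at least 120 immunised: 2% with 1000 women, 51% with 1200.

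**Step 3: what the shortfall costs in power.** Exact two-sided Fisher power is the sum of Bin(x; n1, p1) × Bin(y; n0, 0.00049) over all (x, y) with x/n1 > y/n0 and Fisher p ≤ 0.05.

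Two assumptions have to be made. The ICH risk is taken at 3%, and also at 2%, because the plan says "we took a marge of 1% on the estimated incidence of ICH in FNAIT" and 2% is one reading of that. The number of controls is taken on two bases: 19 per immunised case (the stated 5% share), or 10 per immunised case (one stored control per HPA-1a negative woman, at 10% immunised).

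| Immunised vs controls | Basis | Power at 2% | Power at 3% |
|---|---|---|---|
| 120 vs 2280 | 5% immunised | 77% | 91% |
| 100 vs 1900 | 5% immunised | 70% | 86% |
| 120 vs 1200 | one control per negative woman | 69% | 87% |
| 100 vs 1000 | one control per negative woman | 59% | 80% |

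By the normal approximation, 100 vs 1900 gives 80% at 2% and 89% at 3%.

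**Step 4: a limit on these figures.** The total of 2400 itself could not be reproduced. A two-sided two-proportion or logistic formula at 19:1 gives about 1244–1260 at 3% and 1994–2020 at 2%; with continuity correction it gives 1900 and 2980–3000. The sidedness of the test is not stated. The table therefore shows the size of the change between 120 and 100 cases. It does not restate the plan's own power.

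**Step 5: effect on the incidence endpoint.** The 95% half-width for a 10% immunisation rate is 1.96 × √(0.1 × 0.9 / n): 1.7 percentage points at n = 1200 and 1.9 at n = 1000.

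**The case against.** The strongest reply is that the Ethics and dissemination text is no stopping rule. It gives a planned closing date and a reason to extend it, and nowhere says that recruitment stops at 1000. The range straddles 1200, and its upper end would still leave 1200 after a 20% loss (1500 × 0.8). The primary endpoints are incidences, whose precision hardly changes between 1000 and 1200 women, and at the stated 3% ICH risk 100 cases keep about 80% power or more on either control basis. All of this stands, and it limits the weight of the point. It does not remove the conflict between a stated need of 1200 and a stated goal that 1000 would satisfy.

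A reader might also infer three stronger faults that the article does not support.

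- *That missing consent is not allowed for.* The 50% enrolment assumption removes non-participants before the 60 000 are reached, and Table 1 counts those 60 000 as included. Phase I does type women whose form has not yet arrived, but the later phases require consent, and nothing says that the 1200 or the 1000–1500 counts women without it.
- *That unreturned case report forms are wrongly ignored.* The 1200 contains no inflation, and the surplus in Table 1 (1260 against 1200) is used up by a 4.8% loss. But an allowance of this kind is commonly left to the full protocol, which is not shown, so its absence from an article is no error.
- *That the durations contradict each other.* Study design says "for a period of 2.5 years", while the sample size section says "This would correspond with a study period of 2 years". The second is a projection conditional on 50% enrolment. A longer planned period need not conflict with it: 30 000 a year for 2.5 years would give 75 000 women, 75 000 × 0.021 = 1575 HPA-1a negative and about 158 immunised.

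**Conclusion.** The point holds as an internal inconsistency in the recruitment target. The article requires 1200 HPA-1a negative women, yet states an inclusion goal that 1000 would meet, with about 100 expected immunised cases, 17% below the stated 120. This rests only on the article's own 10% immunisation rate.

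The consequence is moderate. Exact power for the ICH comparison drops by about 5 to 7 percentage points at 3% and 6 to 10 at 2%, depending on how many controls are analysed. A reader might conclude that closing at 1000 leaves the study underpowered, and cite 59% and 80%. Those two figures hold only for Fisher's test with 100 vs 1000. On the plan's stated 5% immunised share they are 70% and 86%, so neither pair should be quoted without its basis. The article also does not show that recruitment would in fact stop at 1000, only that its wording permits it.

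**What to change.** In Ethics and dissemination, replace the range with one minimum that matches the sample size section: at least 1200 consenting HPA-1a negative women with an antibody result and clinical outcome data. Counting women with outcome data deals with unreturned forms without requiring an attrition rate in advance. For orientation, with assumed losses of 5%, 10% and 20%, keeping 1200 usable women means including 1264, 1334 and 1500.

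Check progress at the 1-year interim. Antibody testing and outcome collection follow delivery, so the closing date has to be projected from the completion seen by then.

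If 1000 is to remain acceptable, change the sample size section instead: state the target as about 100 immunised cases and give the power recomputed on the plan's own method, naming the ICH risk, the number of controls and the sidedness of the test.

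The first option is a change of wording to a number already planned. Its only possible cost is a longer inclusion period, which the article already allows. The second costs a recalculation and the publication of a smaller target.

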## Discussion

FNAIT can cause severe bleeding complications in fetuses and neonates, with a high risk of associated morbidity and mortality.^33^ A preventive antenatal treatment, that effectively prevents these bleeding complications from occurring, is available.^5^ In current practice, this prevention is only available in pregnancies with known alloimmunisation, usually after a previously affected child. To prevent these first cases as well, timely detection by prenatal and population-based screening is necessary.

Current lack of prospective non-interventional studies providing data on natural history of the disease as well as a reliable risk assessment tool to identify alloimmunised pregnancies that are at high risk for developing bleeding, complicates the implementation of such population-based screening. The aim of the HIP study is to gather this missing knowledge necessary to adequately evaluate the potential efficacy and feasibility of prenatal population-based screening in order to timely detect and prevent FNAIT-related complications. With the current study design and logistics, making use of the current national screening programme for RBC immunisation with a participation grade of 99.1%. We do not think that selection of RhD-negative and Rhc-negative women would influence the outcome of our study (ie, immunisation rate or bleeding symptoms). RhD and Rhc status has never been associated with platelet immunisation during pregnancy and inheritance is unrelated since the RhD and Rhc genes are located on chromosome 1 and the HPA-1 allele on chromosome 17. Therefore, we expect our results to give an adequate representation of the Dutch population of pregnant women.

A potential limitation of this study protocol is the lack of routine determination of neonatal platelet counts. However, the goals of potential screening and prevention of FNAIT are not to prevent a low platelet count as reflected as a laboratory result, but to prevent symptomatic disease, mainly ICH, with associated morbidity caused by FNAIT. However, routine neonatal cerebral ultrasound is not performed either. Therefore, cases of subclinical ICH without symptoms (such as convulsions or reduced consciousness) or additional bleeding manifestations might be missed, although in theory these might lead to developmental problems later in life. However, major ICHs detected in prospective studies that did perform routine cerebral ultrasound were cases that were symptomatic as well.^19 34^

Further underestimation might occur due to the fact that we will perform only a single screening for anti-HPA-1a alloantibodies, that is, at 27 weeks gestation. Immunisations that occur later in pregnancy or after delivery will not be detected. Also, immunisations that will result in complications and termination of pregnancy or IUFD before 27 weeks gestation will not be identified. However, in terms of assessing feasibility and cost-effectiveness of population-based screening, a slight underestimation is unquestionably preferred to an overestimation. On the contrary, we use another antibody screening method compared with earlier screening studies, which is possibly more sensitive compared with the monoclonal antibody immobilisation of platelet antigens (MAIPA) technique.^35^ The PAK Lx assay was tested on a series with 100 cases with suspected FNAIT by our research group in 2014. In 26 of these cases, anti-HPA-1a was detected by MAIPA, all cases were detected and one more by PAKLx. Overall, to our knowledge, the HIP study will be a unique study to prospectively and observationally collect data on incidence and natural history of FNAIT by including this large number of pregnant women without performing any kind of intervention. Additionally, it will be the first study to be able to identify a unique and unbiased study group, that is, immunised pregnant women without disease and without intervention. This is the pre-eminent group to be used for the development of a risk-assessment platform in order to select immunised pregnancies that are at high risk to develop bleeding complications and would therefore benefit from antenatal preventive measures, such as IVIg treatment.

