## Methods and analysis

### Study objectives

The primary objective of this study is to determine incidence of HPA-1a alloimmunisation and the incidence of clinically relevant HPA-1a-induced FNAIT in the Netherlands. Clinically relevant FNAIT will be defined as minor bleeding (haematoma, bruising, petechiae or small visceral bleeding) and severe bleeding (ICH or internal organ haemorrhage) with the presence of an anti-HPA-1a alloantibody. Additionally, as secondary objective, we aim to collect a set of blood samples that can contribute to the development of a risk assessment model to be used as a diagnostic tool enabling the identification of alloimmunised pregnancies that are at high risk of developing bleeding complications.

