### Study population

For logistic purposes, RhD-negative or rhesus c (Rhc)-negative pregnant women were selected for enrolment in the HIP study. As part of the Dutch prenatal screening programme for infectious disease and erythrocyte immunisation (in Dutch: PSIE), these women are offered a free of charge red cell antibody screening and/or fetal RhD typing at 27 weeks gestation. For this, 9 mL EDTA anticoagulated blood is drawn by their midwife or at certified, local laboratories all over the Netherlands (n=±90) and transported to the Sanquin laboratory in Amsterdam by regular surface mail or private courier service. The programme has a voluntary participation grade of 99%.^22 23^ With approval of the RIVM, that organises this population screening programme, left-over material can be used for the HIP study for HPA-1a typing and stored for further antibody testing after informed consent.

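### The step from RhD- or Rhc-negative women to all Dutch pregnant women is not established: the arguments given leave ancestry, and so the HPA-1a negative rate, open

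*Protocol article*

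**What the plan says.** All references are to the protocol article.

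- **Target.** Study objectives sets the primary aim as to "determine incidence of HPA-1a alloimmunisation and the incidence of clinically relevant HPA-1a-induced FNAIT in the Netherlands".
- **Sample.** Study population states: "For logistic purposes, RhD-negative or rhesus c (Rhc)-negative pregnant women were selected for enrolment in the HIP study".
- **Endpoints.** Study outcomes words the first endpoint more narrowly than the objective: "Incidence of HPA-1a negativity in the RhD-negative or Rhc-negative pregnant population in the Netherlands at 27 weeks of pregnancy". The second is "Incidence of HPA-1a alloantibodies in the tested population at 27 weeks of pregnancy".
- **Planning rate.** Sample size calculation says: "Because 2.1% of the Caucasian population is HPA-1a negative, the total study population should exist of 60 000 pregnant women". Table 1 applies the same 2.1% to the planned cohort of 60 000 and to all 170 000 Dutch pregnancies.
- **Bridge.** The Discussion says that the Rh selection should not affect the immunisation rate or bleeding symptoms. It gives two grounds: no association between Rh status and platelet immunisation has been found, and "inheritance is unrelated since the RhD and Rhc genes are located on chromosome 1 and the HPA-1 allele on chromosome 17". It concludes that "we expect our results to give an adequate representation of the Dutch population of pregnant women". Ancestry is not mentioned there.

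**The concern.** The objective concerns the country, while the data come from roughly a third of its pregnancies, chosen by blood group. Whether one speaks for the other depends on whether Rh type and HPA-1a type are associated in the population. Genes on different chromosomes can still be associated if the frequencies of both vary with ancestry and the population is mixed.

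The first ground, no reported association with platelet immunisation, concerns a later step. The incidence chain starts with HPA-1a negativity, which is the first listed endpoint and the first multiplier in Table 1. The Discussion's statement of what selection should not influence does not name it.

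The study is meant to inform a decision on population screening. The Discussion says that a slight underestimate is preferable to an overestimate for that purpose. If the direction of a possible selection bias is unknown, that preference is not secured, and a larger sample does not help.

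**Working it through.** **Inputs from the article.** HPA-1a negative rate 2.1%, given for the Caucasian population; planned cohort 60 000; about 60 000 eligible women a year; 170 000 pregnancies; immunisation rate about 10% (Sample size calculation and Table 1).

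**The article's own figures.**
- 60 000 × 0.021 = 1260 and 170 000 × 0.021 = 3570, as in Table 1.
- 1260 × 0.10 = 126, as in Table 1.
- Share sampled: 60 000 / 170 000 = 35.3%, which leaves about 65% of pregnancies outside the eligible group.

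**What the chromosome argument leaves open.** Take a two-group mixture. Let *w* be the share of pregnant women outside the Caucasian group, *q* their HPA-1a negative rate, and *r* their chance of being RhD- or Rhc-negative relative to the Caucasian group. The article gives none of these; all three are assumptions.

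- Population rate = (1 − w) × 2.1% + w × q
- Share in the Rh-selected sample: w_s = w·r / (w·r + 1 − w)
- Sample rate = (1 − w_s) × 2.1% + w_s × q
- Difference, sample minus population = (w − w_s) × (2.1% − q)

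The difference is zero only if r = 1 (equal Rh selection) or q = 2.1% (equal HPA-1a frequency). Gene location enters neither condition. For q below 2.1%, the sign depends entirely on r.

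**Worked example, w = 20%, q = 0.5%.** The population rate is 0.8 × 2.1% + 0.2 × 0.5% = 1.78%.
- r = 0.5: w_s = 0.10 / 0.90 = 11.1%; sample rate 1.92%; relative bias +8.0%.
- r = 1.5: w_s = 0.30 / 1.10 = 27.3%; sample rate 1.66%; relative bias -6.5%.

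**Range over w = 10–30% and q = 0–1%.**

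| r | Relative bias in the HPA-1a negative rate |
|---|---|
| 0.25 | +4.0% to +29.0% |
| 0.5 | +2.6% to +17.6% |
| 1 | 0 |
| 1.5 | -2.4% to -13.0% |
| 2 | -4.5% to -23.1% |

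**Scale.** The 95% sampling error on 2.1% of 60 000 is 1.96 × √(0.021 × 0.979 / 60 000) = 0.115 percentage points, or about ±5.5% relative. For the expected 126 immunised women it is about 1.96 / √126 = ±17%.

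**What a comparison of the two Rh strata could detect.** The split is not given, so assume equal halves; an uneven split would be less precise.
- HPA-1a negativity, 30 000 per stratum: 1.96 × √(2 × 0.021 × 0.979 / 30 000) = ±0.23 percentage points on the difference.
- Alloimmunisation, 630 HPA-1a negative women per stratum: 1.96 × √(2 × 0.1 × 0.9 / 630) = ±3.3 percentage points on a rate of about 10%.

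The first comparison is informative. The second is coarse.

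**The case against.** The strongest reply is that the authors do not rely on chromosomes alone. They also cite the absence of any known association between Rh status and platelet immunisation, they say only that they expect the results to be representative, and they already define the first two endpoints in the selected or tested population. Stratified or standardised reporting may also sit in a fuller plan that is not shown.

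Much of this stands. The first endpoint is not biased for the population it names, and the lack of a stratified analysis in a condensed article is not itself a fault. What remains is an inference that the article does state. The no-association ground does not cover how common HPA-1a negativity is, and the chromosome ground does not cover ancestry.

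Stronger readings are tempting but not supported:
- **That the bias is upward.** A reader might infer this from the Caucasian label on the 2.1%. It would need Rh frequencies by ancestry, which the article does not give. Selection is also on either of two Rh types, which could act in opposite directions.
- **That Table 1's 3570 measures the bias.** If the true national rate were below 2.1%, 3570 would be too high. That would come from applying one group's rate to everyone and would arise without any Rh selection.
- **That the leaflet languages show the ancestry mix.** They show translation needs, not shares.

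It is also fair that, for alloimmunisation, sampling error of about ±17% is as large as many of the biases in the table. Bias does not shrink with sample size, but nothing here shows that the study's conclusions would change.

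**Conclusion.** The concern holds in a limited form. The Discussion's claim that the results represent Dutch pregnant women does not follow from the two grounds given. An association between Rh type and HPA-1a type through ancestry is not excluded, and the HPA-1a negative rate in the unsampled 65% or so of pregnancies is assumed, not shown.

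Neither the sign nor the size of any bias can be derived from the article. The range of about -23% to +29% rests wholly on assumed values of w, q and r, and only shows that the bias could exceed the ±5.5% sampling error in either direction. The affected statement is the generalisation to the Netherlands in Study objectives and the Discussion, not the first endpoint as defined in Study outcomes. The correction is inexpensive, changes what may be concluded, and should be made.

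**What to change.** 1. Report HPA-1a negativity, and alloimmunisation among HPA-1a negative women, separately for RhD-negative and Rhc-negative women with confidence intervals. State beforehand how a woman negative for both is classified. A clear difference would contradict the claim that Rh status is irrelevant; similar rates would not prove representativeness.
2. Describe all measured rates as rates in the RhD- or Rhc-negative population. Replace the chromosome argument with a statement that any extrapolation to the Netherlands assumes no association between Rh type and HPA-1a type in the unsampled pregnancies, and list this among the limitations.
3. Give a standardised national rate only if maternal ethnic background is recorded, with the unstandardised rate beside it. Whether it is recorded cannot be seen, because the figure listing the clinical parameters is not shown. Do not weight on Rh strata alone: women positive for both RhD and Rhc are never sampled, so the two strata cannot stand in for them without the assumption in question.

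**Cost.** Items 1 and 2 need only analysis and wording, since Rh type is an inclusion criterion and so known for every woman. The alloimmunisation comparison will be imprecise, with about 126 cases in total, and the national claim becomes more guarded.
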